**Figure 2 figure2:**
[figure not shown]
Study timeline. ADT: advanced diabetes technology; BPA: best practice advisory; IRBL institutional review board; QI: quality improvement; T1D: type 1 diabetes.

##### Refinement

Feedback from the providers at the 7 participating centers will be collected following the implementation of the BPA and periodically during the 12-month assessment period. This feedback will be used to refine the BPA in an iterative fashion.

### Phase 2: Evaluation (Study Design)

Using a nonrandomized matched pair-intervention design (ie, controlled before-after study), we will compare the use of ADT following the BPA intervention among non-Hispanic Black and Hispanic people with T1D at 7 participating T1DX-QI centers. These will be matched with control non-Hispanic Black and Hispanic people with T1D at nonintervention T1DX-QI centers over a 12-month period. Both control and intervention centers have completed the EMR data mapping to the T1DX-QI, allowing for consistent outcome assessment across both groups. The study will consist of 2 distinct periods:

Baseline period (before): 12 months before deployment of the BPA at the intervention centers.Implementation period (after): 12 months after the deployment of the BPA at the intervention centers.

The before-after matched-pair intervention design allows for a real-world assessment of the BPA’s impact on ADT use while controlling for key confounders. Comparing ADT prescribing before and after BPA implementation within intervention sites and using matched controls from nonintervention centers, the design also accounts for site-specific prescribing patterns and secular trends. This quasi-experimental approach is practical for an EMR-based intervention and minimizes selection bias by matching key clinical and demographic variables.

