#### Intervention Centers

A total of 7 T1DX-QI clinical centers, consisting of pediatric and adult diabetes specialty clinics in the United States (Table 2), will participate in both the development and implementation of the BPA. A 7-item Qualtrics survey was distributed to all clinical centers within T1DX-QI to gather information on their EMR systems, capacity to develop automated alerts for CGMs and AIDs, IT capacity and commitment to the project, anticipated EMR freezes or delays during the planned intervention period, typical timeline for EMR changes at the institution, and previous experience building BPAs. Based on these responses, centers were selected to ensure geographical representation of the United States and a balance of pediatric and adult centers, with priority given to clinical centers using Epic EMR and demonstrating capacity, interest, and commitment to the project.

**Table 2 table2:** Intervention clinical centers.

Intervention center	Clinical center	Geographical region	Pediatric or adult
1	Johns Hopkins	Mid-Atlantic	Pediatric and adult
2	Hassenfeld Children’s NYU^a^	Northeast	Pediatric
3	Upstate Medical University	Northeast	Adult
4	Nationwide Children’s	Midwest	Pediatric
5	Grady Memorial	Southeast	Adult
6	University of Texas Southwestern	Southwest	Pediatric
7	Seattle Children’s Hospital	Northwest	Pediatric

^a^NYU: New York University.

Each center will have a designated principal investigator who will participate in monthly meetings with the organizing committee. Johns Hopkins University, which includes both pediatric and adult diabetes centers, will be the primary center for the development of the BPA. This center will oversee prototype development, testing, and postlive validation.

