**Exclusion criteria**
People with type 1 diabetes already using an automated insulin delivery at baseline.Pregnant patients.People with type 1 diabetes receiving end-stage kidney disease dialysis.People with type 1 diabetes using hydroxyurea.

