### Primary Outcome

The primary outcome will be progression in ADT use (as documented in the EMR) during the 12-month study period. For both intervention and control centers, a participant’s baseline ADT status will be ascertained in the 12-month period before deployment of the BPA intervention. The primary outcome will be defined as positive for an individual if any of the following transitions from the baseline period to the implementation period occur with respect to ADT:

No CGM → CGM.No AID → AID.

The T1DX-QI database includes variables that will be used to evaluate the study outcome (eg, medication list and flowsheet data). We have extensively published on the T1DX-QI data source and its validation, and have used the database for several real-world studies [36-42].

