### Analysis

#### Phase 1

For survey data, Likert scale responses will be coded numerically for qualitative analysis. Descriptive statistics will be calculated to summarize the data, and differences between groups (ie, based on demographic variables) will be explored. For the structured interviews and focus groups, a thematic approach will be used to identify, analyze, and report patterns with the qualitative data. NVivo software will be used, which provides features for coding, organizing, and visualizing data [43]. Both deductive and inductive coding methodologies will be used to link similar codes to broader themes based on significant phrases, concepts, and ideas present in the transcripts [44]. Themes will be reviewed and refined through discussions among the research team to ensure consistency and reliability.

#### Phase 2

The primary outcome will evaluate the impact of the BPA intervention on patients’ progression of ADT use using a generalized linear mixed model to account for matched pairs and random center effects. The model will be adjusted for the number of encounters and other possible confounders not already matched.

The secondary outcome analyses will compare differences in ADT use between non-White and White people with T1D in the intervention and control groups. Additional secondary and exploratory outcomes will be assessed using the appropriate statistical model for the outcome adjusting for patient- and center-level confounders. Exploratory analysis assessing pediatric and adult centers separately will be performed.

In cases where ADT is not prescribed by the provider, we will explore the reasons why, and why the diabetes technology was not offered or accepted by patients. We will quantify the BPA responses as provider-led or patient-led reasons for not advancing ADT use. We will perform multivariable logistic regression analysis to evaluate whether patient characteristics (demographics, race, ethnicity, diabetes characteristics, and complications) are associated with the reasons that technologies are not offered or declined.

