The use of a BPA as a CDS tool in this protocol serves as an intervention at both the provider and system level, enabling greater scalability to create lasting improvements in ADT uptake and glycemic outcomes. There is previous evidence supporting the successful implementation of computer-based decision support in diabetes care [49-51]. One cluster randomized clinical trial consisting of 14 primary care centers (66 primary care physicians and 697 patients with T2D on insulin therapy) in Madrid, Spain successfully implemented a computer application designed to help primary care physicians make decisions about insulin therapy [52]. The design of the algorithm included the recommendation to change the insulin dose and the insulin regimen when necessary. The people receiving care at the 7 centers randomly assigned to use the algorithm had a significant reduction in HbA_1c_ compared with the people at the 7 centers in the control group [52]. Another meta-analysis of 70 randomized controlled trials assessing the critical features of CDS systems that improve clinical practice highlighted 4 initiatives strongly associated with a successful center decision support system: (1) CDS provided automatically as part of clinical workflow, (2) CDS delivered at the time and location of decision-making, (3) actionable recommendations provided such as prescriptions, and (4) computer-based [53]. In this protocol, the BPA is designed to incorporate these 4 critical features and thus we expect to see improvement in ADT uptake at the intervention sites.

This study leverages the T1DX-QI consortium, which has a robust quality improvement and health equity framework to evaluate the impact of an EMR-based BPA on ADT use and racial disparities. By implementing the intervention at 7 motivated sites with strong research and QI expertise, and strong IT infrastructure, the study ensures effective troubleshooting and optimization of the BPA. This real-world, multicenter approach enhances generalizability and supports the potential for scalability to other centers if successful. In addition, integrating health equity principles strengthens the study’s ability to assess disparities and inform broader systemic improvements in diabetes care.

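### The design is credited with a within-site before-after comparison, but the primary outcome is a single post-deployment transition per patient, so residual differences in center progression rates would be attributed to the BPA

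*Protocol article*

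**What the plan says.** Phase 2: Evaluation (Study Design) labels the study a controlled before-after study with two 12-month periods. It describes "Comparing ADT prescribing before and after BPA implementation within intervention sites and using matched controls from nonintervention centers" and concludes that "the design also accounts for site-specific prescribing patterns and secular trends". The same section states the comparison itself as one made after deployment: "we will compare the use of ADT following the BPA intervention among non-Hispanic Black and Hispanic people with T1D", set against matched patients at nonintervention centers.

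The other sections bear on this as follows:

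- **Primary Outcome:** "The primary outcome will be progression in ADT use (as documented in the EMR) during the 12-month study period". It is positive if a patient moves from no CGM to CGM, or from no AID to AID. The 12 months before deployment serve to establish starting status.
- **Eligibility:** the exclusions include "People with type 1 diabetes already using an automated insulin delivery at baseline". Patients on CGM alone remain eligible.
- **Analysis, Phase 2:** the effect is estimated "using a generalized linear mixed model to account for matched pairs and random center effects", with adjustment for the number of encounters and for confounders not already matched.
- **Control Group:** the propensity model includes center size, staffing, location, patient demographics and historical CGM and AID usage rates. Balance is judged by standardized mean differences below 0.1.
- **Intervention Centers:** sites were chosen for geographic spread and pediatric/adult balance, with priority for those on Epic and "demonstrating capacity, interest, and commitment to the project". The Discussion adds: "By implementing the intervention at 7 motivated sites with strong research and QI expertise".

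**The concern.** To account for a site's own prescribing pattern, a before-after design needs the same quantity measured in both periods. Here the quantity is 12-month progression, and it is defined only for the implementation year. AID uptake during the baseline year cannot stand in for it, because patients already using AID at baseline are excluded in both groups.

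The BPA is deployed by center, so no center supplies both exposed and unexposed outcomes. A random center effect widens the standard error to reflect variation between centers, but it cannot separate a systematically higher underlying rate at the 7 selected centers from an effect of the BPA.

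At stake is attribution. If the intervention centers would have progressed faster anyway, in ways the matching does not capture, the primary estimate includes that difference and nothing in the stated outcome or model would reveal it.

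**Working it through.** **1. The plan's own sample-size figure.** The Power section gives 589 matched pairs for 90% power at a 5-point difference, with a control rate of 15%. Alpha is not stated; I assume 0.05 two-sided. A one-sample formula reproduces it:

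n = (1.960·√(0.15·0.85) + 1.2816·√(0.20·0.80))² / 0.05² = 588.03, rounded up to 589.

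This is not the only route. One-sample 20% against 25% at one-sided 0.05 gives 588.42, also 589. Neither calculation contains a before-period term.

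**2. What the contrast estimates.** Suppose the BPA does nothing and intervention centers progress b points faster than the 15% control rate in both years, after matching.

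- Post-deployment contrast: (15 + b) − 15 = b.
- Difference of before-after changes: [(15 + b) − (15 + b)] − [15 − 15] = 0, provided the gap is stable over time.

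So the bias equals b, point for point. The documents give no value for b; 1 to 5 points is an assumed range.

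**3. How often an ineffective BPA would look effective.** Inputs: 3000 intervention patients (Abstract), 1:4 matching (Control Group), 15% control rate (Power). Normal approximation for two proportions, pooled standard error for the test and unpooled for the estimate, no center variation. For b = 2 points:

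- pooled rate = (3000·0.17 + 12,000·0.15)/15,000 = 0.154
- pooled SE = √(0.154·0.846·(1/3000 + 1/12,000)) = 0.00737
- unpooled SE = √(0.17·0.83/3000 + 0.15·0.85/12,000) = 0.00759
- probability = Φ((0.02 − 1.96·0.00737)/0.00759) = 0.77

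Now allow for center effects with an assumed between-center SD τ, 7 intervention centers and 41 control centers (Results):

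SE = √(τ²(1/7 + 1/41) + 0.1275(1/3000 + 1/12,000)), where 0.1275 = 0.15·0.85.

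| Assumed gap b | No center variation | τ = 2 points | τ = 4 points |
|---|---|---|---|
| 1 point | 0.28 | not run | not run |
| 2 points | 0.77 | 0.45 | 0.20 |
| 3 points | 0.98 | 0.78 | 0.39 |
| 5 points | 1.00 | 0.995 | 0.80 |

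Center effects make a false positive less likely, but the estimate stays displaced by b.

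**4. Sampling cost of a before-after contrast.** Two-sided 0.05, 90% power, equal groups, independent period samples, no clustering; 15% and 15% before, 15% and 20% after. (1.960 + 1.2816)² = 10.507.

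- Post-deployment only: (0.1275 + 0.16)·10.507/0.05² gives 1209 per group.
- Group by period: (3·0.1275 + 0.16)·10.507/0.05² gives 2281 per group per period.
- Ratio: 0.5425/0.2875 = 1.89.

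**The case against.** Four arguments on the other side have weight.

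- **Secular trends.** A reader might infer that these are uncontrolled. The documents do not support that. Controls are followed over the same period, so a trend shared by both groups cancels without any baseline contrast. Only trends that differ between groups remain.
- **Matching.** A reader might also infer that every pre-existing center difference passes into the estimate. That is too strong. The propensity model includes several center traits and historical CGM and AID usage, with a balance check, and the model adjusts for further confounders. What remains is that historical usage is a level of use, not the rate at which non-users progress over 12 months. Motivation, IT capacity and QI expertise are not named among the matching variables.
- **Center selection.** The documents do not say that the 7 centers progress faster. Geography and pediatric/adult balance also governed the choice, and the Discussion's limitations attribute greater motivation to T1DX-QI centers in general, which includes the controls. Chance variation among 7 centers is not bias either; the random center effects carry it into the standard error.
- **Model detail.** Model terms may sit in a statistical analysis plan that is not shown, so the absence of a period term in a short article proves little. The point rests instead on the outcome definition: a group-by-period term needs a before-period outcome, and none is defined. The argument from the AID exclusion is also limited to AID, since baseline CGM status does vary among eligible patients.

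**Conclusion.** The point holds in limited form. The design section claims a within-site before-after comparison that the primary outcome and stated model do not contain. The concurrent matched comparison is legitimate and handles shared trends and part of the center difference. Residual, unmatched differences in 12-month progression rate, and trends that differ between groups, would be attributed to the BPA.

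The direction and size of that bias cannot be derived from the documents. A gap of 1 to 5 points is an assumption chosen to show scale; at 5 points it would equal the smallest effect planned for. The false-positive probabilities also depend on the assumed between-center SD, the two-sided 0.05 level and the stated patient numbers.

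This should be fixed because it affects how far the primary estimate can be credited to the BPA. It does not show that the estimate is biased or that the design is unusable.

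**What to change.** From T1DX-QI data, compute each center's progression in the 12 months before deployment, for both groups, among patients who were AID-free at the start of that period. Then do one of the following:

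1. **Prior rate as covariate.** Include that center progression rate in the propensity model and as a covariate in the primary mixed model. This is the lighter change.
2. **Group-by-period contrast.** Where 24 months of pre-deployment data exist, build the earlier cohort under the same eligibility rules and re-match it. Fit group, period and group by period, with center, center-by-period and patient random effects (patients who stay AID-free appear in both periods). Make the interaction the primary effect and state the assumption that the gap between groups would otherwise have been stable.
3. **If neither is done,** reword the design sentence so that it claims only a concurrent matched post-deployment comparison.

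Options 1 and 2 cost one further extraction of existing data. Option 2 also needs about 1.9 times the sample: 2281 rather than 1209 per group per period before clustering. That is within the roughly 3000 intervention patients expected, if the prior year supplies similar numbers. The Power section drew a control progression rate from one earlier 12-month period, which shows that such a rate can be computed. It does not establish that 24 months of pre-deployment data exist at all 7 intervention centers, so this must be confirmed before option 2 is chosen.

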### Eligibility Criteria

Inclusion and exclusion criteria are listed in Textbox 1.

Inclusion and exclusion criteria.
**Inclusion criteria**
Age ≥2 yearsA diagnosis of type 1 diabetes (determined using *ICD-10* [*International Statistical Classification of Diseases and Related Health Problems, Tenth Revision*] diagnosis codes [E10.X] and other various discrete data elements, such as flowsheet rows, as mapped by clinical centers to the Type 1 Diabetes Exchange Quality Improvement Collaborative database).Receiving care at one of the seven intervention centers or a matched control center in the Type 1 Diabetes Exchange Quality Improvement Collaborative.Patients with at least one clinical encounter (in-person or video visit) in both the baseline and follow-up periods.Not prescribed an automated insulin delivery system (patients prescribed only continuous glucose monitoring are eligible, provided they are not prescribed an automated insulin delivery system).
**Exclusion criteria**
People with type 1 diabetes already using an automated insulin delivery at baseline.Pregnant patients.People with type 1 diabetes receiving end-stage kidney disease dialysis.People with type 1 diabetes using hydroxyurea.

### Intervention Group

People with T1D meeting the eligibility criteria at one of the 7 intervention centers where the BPAs are deployed will be assigned to the intervention group. We estimate that there are approximately 11,496 eligible people with T1D in the intervention centers.

### Control Group

Matched control people with T1D will be selected from the pool of nonintervention clinical centers sharing EMR data with the T1DX-QI coordinating center with over 80,000 people with T1D data available in the database.

To accurately match people with T1D between the intervention and control groups, we will identify and include a comprehensive set of covariates that may influence the likelihood of receiving the BPA. These covariates will include both patient-level and clinical center-level characteristics. Patient-level characteristics will include demographics (age, sex, race, and ethnicity), socioeconomic status (insurance type and zip code–based income), and clinical characteristics (duration of diabetes, comorbidities, HbA_1c_ levels, etc). Clinical center-level characteristics will include clinic size and resources (number of people with T1D seen annually, number and type of clinical full-time equivalents, geographic location, patient population demographics, and historical usage rates of CGMs and AID systems. Intervention and control groups will be matched using the propensity score method.

Before propensity score matching, any missing baseline covariate data will be imputed using predictive modeling techniques. Multiple imputation by chained equations will be used to generate multiple complete datasets, which will then be averaged to create a single dataset for the matching process. This approach ensures that the imputed values are based on observed data, maintaining the integrity and representativeness of the dataset.

Propensity scores will be estimated using logistic regression, where the outcome variable is the likelihood of receiving the BPA intervention. The model will include the identified patient-level and clinical center–level covariates as predictors. The estimated propensity score represents the predicted probability that a given patient would receive the BPA based on their covariate profile. Patients in the intervention group will be matched to patients in the control group using a 1:4 matching ratio. Nearest neighbor matching without replacement will be used, ensuring that each control patient is only matched once. The matching process will aim to minimize the distance between propensity scores of matched pairs, thus creating comparable groups. The quality of the matching process will be assessed by comparing the distribution of covariates between the matched intervention and control groups. Standardized mean differences will be calculated for each covariate to ensure balance, with a standardized mean difference of less than 0.1 indicating adequate balance. In addition, a visual inspection of propensity score distributions before and after matching will be conducted to confirm the success of the matching process.

To assess the robustness of the results, sensitivity analyses will be performed using different matching algorithms (eg, caliper matching and kernel matching) and varying the matching ratio (eg, 1:3). In addition, the impact of imputation on the results will be examined by comparing outcomes using datasets with and without imputed values.

For nonstatic matching variables (eg, laboratory results), the last available result in the baseline period of 12 months before the BPA deployment date in the intervention centers will be used.

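### Averaging the multiply imputed datasets into one before propensity matching turns multiple imputation into near conditional-mean single imputation and drops the between-imputation variance

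*Protocol article*

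**What the plan says.** The protocol article, Control Group, states that "any missing baseline covariate data will be imputed using predictive modeling techniques". It names the method: "Multiple imputation by chained equations will be used to generate multiple complete datasets". These are then combined before anything else is done, since they are "multiple complete datasets, which will then be averaged to create a single dataset for the matching process". The reason given is: "This approach ensures that the imputed values are based on observed data, maintaining the integrity and representativeness of the dataset".

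The covariates concerned include "demographics (age, sex, race, and ethnicity), socioeconomic status (insurance type" and zip-code income), together with diabetes duration, comorbidities and HbA1c. The list therefore mixes continuous, binary and unordered multi-level variables.

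The same section then fits one logistic propensity model and forms one matched set: "Nearest neighbor matching without replacement will be used, ensuring that each control patient is only matched once". Balance is judged by standardized mean differences (SMDs) below 0.1. The only check on imputation is a comparison of outcomes with and without imputed values. Under Analysis, Phase 2, the primary outcome is analysed with one generalized linear mixed model. No pooling across imputations is mentioned there, and none is possible once the datasets have been collapsed.

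**The concern.** Multiple imputation draws several plausible values for each missing entry so that analyses of the completed datasets differ, and the differences measure what is not known. Averaging the entries first removes those differences. Three consequences follow.

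- **Categorical covariates.** The mean of several drawn categories is usually not a category.
- **Continuous covariates.** Averaged imputations move towards the conditional mean given the patient's other data, so the imputed patients vary too little.
- **Uncertainty.** With one completed dataset there is no between-imputation variance to add to the standard error.

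This matters because the study is not randomized and relies mainly on matching to control confounding. The averaged values feed the propensity score and so decide which controls are selected. The article also presents the step as a strength, "maintaining the integrity and representativeness of the dataset", although averaging reduces spread and blurs category membership.

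**Working it through.** The plan gives no figure to reproduce. The number of imputations m, the missing share f and the predictability of the covariates are all unstated, so every value for them below is an assumption.

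**1. Binary covariates.** If a missing 0/1 value is drawn m times with probability p, the mean is neither 0 nor 1 with probability 1 − p^m − (1 − p)^m. For m = 10 and p = 0.10 this is 1 − 0.10^10 − 0.90^10 = 0.65.

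| m | p = 0.05 | p = 0.10 | p = 0.30 | p = 0.50 |
|---|---|---|---|---|
| 5 | 0.23 | 0.41 | 0.83 | 0.94 |
| 10 | 0.40 | 0.65 | 0.97 | 0.998 |
| 20 | 0.64 | 0.88 | 0.999 | 1.00 |

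For unordered categories with more than two levels the average of the codes has no meaning. If three insurance types were coded 1, 2 and 3, draws split evenly between 1 and 3 would average to 2, a type that no draw proposed.

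**2. Continuous covariates.** Scale the covariate to variance 1 and let the other variables explain a share R². One draw is the conditional mean plus a residual of variance 1 − R². The mean of m draws has variance R² + (1 − R²)/m. With R² = 0.30 and m = 20 this is 0.30 + 0.70/20 = 0.335. If patients with missing and observed values have the same mean, the overall loss is f × (1 − 0.335):

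- f = 10%: 0.10 × 0.665 = 6.7%
- f = 20%: 0.20 × 0.665 = 13.3%
- f = 40%: 0.40 × 0.665 = 26.6%

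With m = 5 instead, the retained variance is 0.30 + 0.70/5 = 0.44, and f = 20% gives 0.20 × 0.56 = 11.2%.

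**3. Standard error.** Rubin's total variance is W + (1 + 1/m)B, where W is the within- and B the between-imputation variance. With one averaged dataset B cannot be estimated and is in effect set to zero.

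**4. Illustrative simulation.** Assumptions: 4,000 patients, one binary confounder missing at random, m = 10, treatment and outcome in the imputation model, 1:2 nearest-neighbor matching, true risk difference 0.05, a simple two-group variance and 150 replicates.

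| Missing (about) | Estimate, averaged | Estimate, pooled | SE, averaged | SE, pooled | Ratio of SEs |
|---|---|---|---|---|---|
| 10% | 0.0506 | 0.0486 | 0.0176 | 0.0181 | 0.97 |
| 20% | 0.0536 | 0.0495 | 0.0176 | 0.0182 | 0.97 |
| 40% | 0.0601 | 0.0507 | 0.0175 | 0.0186 | 0.94 |

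The averaged SE is 3% to 6% below the pooled one and does not rise with missingness. The averaged estimates had replicate standard deviations of 0.0174, 0.0193 and 0.0188. Dividing by √150 = 12.2 gives simulation errors of about 0.0014, 0.0016 and 0.0015. The departures from 0.05 are 0.0006, 0.0036 and 0.0101, or about 0.4, 2.3 and 6.6 of those errors. The drift is within noise at 10% missing and clear at 40%.

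**5. Balance check.** In the same simulation the SMD on the averaged covariate was 0.003, 0.011 and 0.014. On the true covariate, in the same matched sets, it was 0.009, 0.018 and 0.041. The check reports the first set of numbers, not the second.

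**The case against.** The averaged dataset is made for matching, and the outcome model is to adjust for confounders that matching has not covered. Imputed covariates therefore act mainly through the choice of controls, and the SE shortfall in the illustration is small. That stands. It is also only a comparison with the pooled SE. The estimates varied between replicates about as much with complete data (0.0178, 0.0191, 0.0193) as with averaged data, so 150 replicates cannot show how far true coverage falls. The bias figures depend on one assumed confounder and on having the outcome in the imputation model, which the article does not specify.

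Four stronger readings are tempting, and the documents do not support them.

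- **All averaged values are impossible.** Only categorical covariates are affected in this way. An averaged HbA1c or duration is a possible value with too little spread. A logistic model will also accept a fractional 0/1 indicator, though not as an observed category.
- **Averaged race or ethnicity decides who is in the study population.** Phase 2 compares non-Hispanic Black and Hispanic patients, but nothing says that imputed values determine membership. A patient with neither recorded may simply not qualify.
- **Shrunken spread makes the SMD check lenient.** With an unchanged mean difference, a 13.3% variance loss multiplies the SD by √0.867 = 0.931, so an SMD of 0.100 becomes 0.100/0.931 = 0.107. Reduced spread alone makes the check stricter. The sound point is that the check describes the wrong values.
- **Averaging worsens true balance.** The illustration does not show this. Every true-covariate SMD after averaging was below 0.1, while matching within imputations gave 0.046, 0.088 and 0.179.

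The comparison with and without imputed values is a partial safeguard, since it could reveal that results depend on imputation. Neither side of it is a pooled analysis, so it cannot supply the missing variance component.

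**Conclusion.** The point holds and should be fixed. The article fixes a procedure that defeats the purpose of the method it names, so this is not a detail left to a fuller plan. Fractional or meaningless categorical values, reduced spread in imputed continuous values and the loss of between-imputation variance follow from the averaging itself, whatever the inputs.

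The size of the harm cannot be established from the documents. Under R² = 0.30, m = 20 and 20% missing, a continuous covariate loses about 13% of its variance. In the illustration the SE was 3% to 6% below the pooled value. Bias was negligible at about 10% missing and about 0.01 on a true 0.05 at about 40%. The fair statement is that the estimate may be biased and its standard error understated by an unknown amount, probably little if few values are missing. A claim that the trial's matching and intervals are materially wrong goes further than the documents allow.

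**What to change.** Replace the averaging step as follows.

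- State the number of imputations, and impute each categorical covariate with a model that returns real categories.
- Within each imputed dataset, estimate the propensity score, match, check SMDs and fit the primary mixed model.
- Pool the effect estimates and their variances by Rubin's rules, and summarize balance across the imputed datasets.
- Delete the statement that averaging maintains integrity and representativeness.

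If one matched set is essential, propensity scores could instead be averaged across imputations, with covariates kept in their own categories, but the analysis must then account for imputation variance separately.

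The cost is more than wording: extra computing, m matched sets to report instead of one, and a rule for how the possible addition of matched pairs after an interim look (Power section) works when there are m sets. No new data are needed.
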